### Control group

Patients in the control group have at least three interviews with a research assistant. Completing the measures and taking part in the interview gives them an opportunity to talk about their feelings. The extent to which they feel that this is therapeutic is explored in the follow-up interviews.

### Recruitment procedure

The recruitment and follow-up procedure is shown in Figure 1. Potential participants are identified by palliative care teams from their lists. For patients recruited from one NHS Trust, these are in-patients or those visiting out-patient clinics. The research assistant gives potential participants an invitation letter and patient information sheet after being introduced by the palliative care team. The research assistant visits patients at least 24 hours later to find out if they are interested in taking part. From the other Trust we are recruiting patients cared for in the community. The clinical nurse specialist visiting the patient will give them the invitation letter and patient information sheet. They will be asked to send a reply slip to the research team or to notify the Clinical Nurse Specialist of their decision to take part or not. Patients are encouraged to discuss involvement in the study with family or friends before deciding whether or not to take part.

**Figure 1 F1:**
[figure not shown]
**Recruitment and follow-up procedure**.

Before consent is taken from patients who have expressed an interest in taking part, the research assistant checks they have fully understood the patient information sheet before obtaining written consent from those who are willing to take part. As a final check patients are screened with the Blessed Orientation Memory Concentration Test [8] to assess cognitive functioning after the consent procedure. It has been suggested by [name] (personal communication) that Dignity Therapy is not suitable for patients with a score equal to or greater than 15. In such cases patients are excluded. This is done sensitively: the research assistant spends some time chatting with them about neutral topics. This approach has worked successfully in a previous study[9]. The proportion of patients excluded at this stage will be reported. Oncologists in the Trusts have been informed of the study and General Practitioners will be informed of their patients' involvement.

Following the consent procedure, participants are asked to complete the baseline measures. They are then randomized. Those in the intervention group are given the framework of therapy questions (Appendix 1) so that they have an opportunity to think about their answers before the therapy interview. The therapist arranges to conduct the dignity therapy interview as soon as possible after recruitment (usually within two to three days), in the location most suited to the patient and in the most private area available if they are in hospital. Since the condition of participants could fluctuate rapidly, the timing of the contacts are sometimes adjusted and meetings rescheduled. If a participant's condition deteriorates, meetings are rescheduled up to three times before sensitively excusing them from the study. This, and the feasibility of following up with people if they leave hospital, will also be reported and taken into account when developing the RCT. Participants in the control group are reminded that they will still have the opportunity to talk to the researcher about how they are feeling and about their views on taking part in the study.

At recruitment the research assistant asks participants to nominate a close family member or friend who is invited to take part in a telephone interview. For patients in the intervention group the nominated family member or friend is often the recipient of the 'generativity' document, however, if the participant mentions other recipients they will also be invited for interview. Participants are not excluded if they do not nominate a family member or friend. We contact the palliative care teams to determine when a participant has died and conduct interviews three months post bereavement with all nominated family and friends and any additional recipients of the document.

### Outcomes

Both quantitative and qualitative outcomes are assessed (Table 1). These are collected from patients by face-to-face interviews at two time-points: approximately one (T2) and four weeks (T 3) after the dignity document has been completed, and the equivalent in the control group. This longer-term follow-up has not been included in the previous evaluation of Dignity Therapy, or in the current trials being conducted by [name] and colleagues. However, we believe it is important to evaluate the longer-term impact of the intervention. The feasibility of doing this is explored as part of this feasibility study. Quantitative measures have been validated and are fairly quick and easy to use. Qualitative interview schedules have been developed for the study.

**Table 1 T1:** Measures for each time point

	**Patients**		**Family/friends**	
	Intervention	Control	Intervention	Control
**At patient recruitment**				
Patient characteristics	x	x		
Patient Dignity Inventory^10^	x	x		
Herth Hope Index^13^	x	x		
Hospital Anxiety & Depression Scale^11^	x	x		
Distress Thermometer^12^	x	x		
EQ-5D^14 ^(Quality of life)	x	x		
Two item measure of quality of Life	x	x		
Palliative Care Outcome Scale^15^	x	x		
**As soon as possible post intervention**				
Acceptability of therapy/study (interviews)	x	x	x	x
Patient Dignity Inventory^10^	x	x		
Herth Hope Index^13^	x	x		
Hospital Anxiety & Depression Scale^11^	x	x		
Distress Thermometer^12^	x	x		
EQ-5D^14 ^(Quality of life)	x	x		
Two item measure of quality of Life	x	x		
Palliative Care Outcome Scale^15^	x	x		
**One month post intervention**				
Acceptability of therapy/study	x	x		
Patient Dignity Inventory^10^	x	x		
Herth Hope Index^13^	x	x		
Hospital Anxiety & Depression Scale^11^	x	x		
Distress Thermometer^12^	x	x		
EQ-5D^14 ^(Quality of life)	x	x		
Two item measure of quality of Life	x	x		
Palliative Care Outcome Scale^15^	x	x		
**Three months post bereavement***				
Hospital Anxiety & Depression Scale^11^			x	x
Complicated Grief assessment^20^			x	x
Acceptability of therapy/study			x	x
Palliative Care Outcome Scale^15^			x	x

* It is likely that it will not be possible to collect post bereavement outcomes from all the recipients of the legacy documents within the relatively short timeframe of this pilot study. However, in depth qualitative data on their views of the therapy, taking part in the study and completing the outcome measures will be obtained from those who are interviewed.

#### Main outcome for patients

The primary outcome is patients' sense of dignity (potential effectiveness). This is assessed at baseline, (T1) and at T2 and T3 follow-ups, using the Patient Dignity Inventory[10]. This measure evolved directly from the dignity model, therefore, questions correspond to each of the model themes and sub-themes, including: physical, psychosocial, existential and spiritual domains of concern or distress. This measure has been validated in Canada and has been shown to have excellent face, internal, test-retest and concurrent validity.

#### Secondary outcomes for patients

Potential effectiveness is also assessed using: the Hospital Anxiety and Depression scale[11] and the distress thermometer [12] (psychological distress); the Herth Hope Index[13] (hopefulness); the EQ-5D[14], the POS (Palliative Care Outcomes) [15] and a two item measure used by [name] in the current trials of Dignity Therapy (both quality of life). To assess feasibility of delivering Dignity Therapy in this setting, time taken to organize and conduct the Dignity Therapy sessions, transcribe and edit narratives, deviations from the therapy protocol and uncompleted interventions and the reasons, and the therapist's perceptions of competence as a result of training are recorded. To assess the acceptability of Dignity Therapy we are conducting semi-structured interviews with participants in the intervention group to obtain their views on the intervention. The therapist is recording her experiences of delivering the therapy and her observations of patient's responses during and after the therapy. As suggested by Ferrell[16], we are reporting case studies of any difficult cases.

#### Demographic measures

Demographic information is collected, including: cognitive functioning (using the Blessed Orientation Memory Concentration test[8]), co-morbidity (using the Comorbidity Index and Scores of Charlson[17]), performance status (using Karnosfsky scores[18], and ability to perform activities of daily living (Barthel scores[19]), age, gender, ethnic group.

#### Outcome measures for family/friends/recipients of 'generativity' documents

In completion of the therapy, semi-structured telephone interviews are conducted with patients' family/friends and other recipients of the 'generativity' documents to obtain their perceptions of the impact of the intervention, on themselves and on the patient (intervention group), and their views on taking part in the study (both groups). For patients who die during the data collection period of the study, follow-up telephone interviews are conducted with family/friends/recipients of the 'generativity' documents at three months post bereavement. As in the initial interview, these cover their perceptions of the impact of the intervention, on themselves and on the patient, and their views on taking part in the study. They are also asked to complete the Complicated Grief Assessment[20], which is used to screen for complicated grief reactions and the Hospital Anxiety and Depression Scale [11]. The questionnaire is mailed to them after the telephone interview along with a pre-paid envelope in which to return it. Their age, gender, ethnic group and relationship to patients are also recorded.

#### Piloting methods for a Phase III trial

Time taken to obtain informed consent and collect outcomes, exclusions, recruitment and drop-out rates (patients and their family and friends) are recorded. In addition their views on taking part in the study (e.g. being randomized) are sought in qualitative interviews, and their views on completing the outcome measures are recorded when they are completing them. Any problems with completing measures will be reported, including missing data.

### Analyses

#### Quantitative data

In view of the relatively small sample size, analyses will be mainly descriptive, however, between and within participant comparisons of outcomes will be conducted and the appropriate effect size estimates reported. Either parametric or non-parametric tests will be used, depending on the distribution of the data. The intervention and control group will be compared on the main outcome (a sense of dignity) and secondary outcomes (distress, hopefulness, quality of life and palliative care outcomes). We will also compare Time 2 and Time 3 follow-up with baseline for both groups on these measures, using a paired test. The two groups will also be compared on demographic characteristics and baseline measures. We will also report recruitment rates and compare drop-out rates and missing data in the two groups.

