## Methods

### Study design

A Phase II open-label RCT comprising two groups: (i) Intervention (Dignity Therapy offered in addition to standard care), and (ii) Control group (standard care). Standard care comprises assessment by a multi-professional palliative care team, including nurses, a psychosocial worker and doctors trained in providing psychosocial support. Consenting participants have been randomly allocated to one of these two groups after baseline (T1) measures have been collected.

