### Randomization

Randomization was conducted by an independent statistician. Treatment allocation (Dignity Therapy or control) was performed by block randomization with a fixed block size of two. Allocation concealment is facilitated by using sequentially numbered opaque sealed envelopes for consecutive and eligible participants. To reduce the risk of bias, the research assistant opens the next envelope in the presence of the patient to ascertain which group the patient has been allocated to after baseline measures have been collected from participants.

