### Participants

The sample will comprise 40 adults with advanced cancer who have been referred to hospital-based palliative care teams working in two NHS Trusts, and who are well enough to participate in a protocol lasting two weeks. For this pilot study, we are obtaining in-depth information on taking part in the study and receiving the therapy from a relatively small sample rather than planning to detect significant group differences. One of the aims of the study is to estimate the effect size for an RCT.

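### The stated between-group PDI comparison lets the data choose the test and gives baseline PDI no role, which may cost avoidable precision in the effect estimate

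*Protocol article*

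**What the plan says.** Only the protocol article is available.

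- **Between-group analysis** (Analyses, Quantitative data): "The intervention and control group will be compared on the main outcome (a sense of dignity) and secondary outcomes". On method: "Either parametric or non-parametric tests will be used, depending on the distribution of the data". No model, covariate or time structure is attached to the between-group comparison. Effect sizes are promised, and the analysis is described as largely descriptive.
- **Primary outcome** (Main outcome for patients): "This is assessed at baseline, (T1) and at T2 and T3 follow-ups, using the Patient Dignity Inventory".
- **Timing of baseline** (Study design): "Consenting participants have been randomly allocated to one of these two groups after baseline (T1) measures have been collected".
- **Stated uses of baseline**: paired tests of T2 and T3 against baseline within each group, and a comparison of the two groups at baseline (both in Quantitative data). Inclusion criteria adds an exploration of whether baseline distress and loss of dignity moderate the effect.
- **Size and purpose** (Participants): "The sample will comprise 40 adults with advanced cancer who have been referred to hospital-based palliative care teams". The trial collects in-depth information "from a relatively small sample rather than planning to detect significant group differences", and "One of the aims of the study is to estimate the effect size for an RCT".

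**The concern.** The main quantitative product of this pilot is an estimate to carry into a Phase III design, so precision and a clearly defined effect measure matter more than a p-value. Two features of the stated method work against that.

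First, none of the three stated uses of baseline PDI improves the between-group estimate. A paired test within one arm mixes any treatment effect with the course of the illness. A balance comparison can show a chance difference between arms but does not correct for it. A moderation analysis asks a different question.

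Second, the choice between a parametric and a rank test is left to the observed distribution. About 20 patients per arm are a weak basis for that judgement. The effect measure regarded as appropriate may follow the test, so it stays open until the data are in.

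At stake is a wider interval around the PDI effect than the collected data require.

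**Working it through.** The article gives no alpha, SD, target difference, power or drop-out rate for the 40 patients, so there is no figure of its own to reproduce. The check compares the precision of the two analyses in units of the follow-up PDI SD.

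**Inputs**
- N = 40, from Participants.
- n = 20 per arm, from two groups and "block randomization with a fixed block size of two".
- r, the correlation of baseline with follow-up PDI: not given. Assumed 0 to 0.7.
- Numbers analysed: 40. For attrition, 30 and 20 are assumed as illustrations.

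**Formulas**
- Unadjusted: SE = √(2/n). Half-width = t(0.975; N − 2) × SE.
- ANCOVA on baseline: SE = √(2/n) × √[(1 − r²)(1 + 1/(N − 4))]. Half-width = t(0.975; N − 3) × SE. The factor 1 + 1/(N − 4) is the expected cost of estimating the covariate slope.
- Equivalent unadjusted sample: N / [(1 − r²)(1 + 1/(N − 4))].

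**Worked case, N = 40**
- Unadjusted: SE = √(2/20) = 0.316. Half-width = 2.024 × 0.316 = 0.640.
- ANCOVA, r = 0.6: SE = 0.316 × √(0.64 × 1.0278) = 0.256. Half-width = 2.026 × 0.256 = 0.520.
- Equivalent sample at r = 0.6: 40 / (0.64 × 1.0278) = 60.8.

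**Results, N = 40 (unadjusted half-width 0.640 SD)**

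| Assumed r | Adjusted half-width (SD) | Ratio to unadjusted | Equivalent unadjusted N |
|---|---|---|---|
| 0 | 0.650 | 1.015 | 39 |
| 0.3 | 0.620 | 0.968 | 43 |
| 0.5 | 0.563 | 0.879 | 52 |
| 0.6 | 0.520 | 0.812 | 61 |
| 0.7 | 0.464 | 0.725 | 76 |

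**With attrition (half-widths, SD)**

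| Analysed | Unadjusted | r = 0 | r = 0.3 | r = 0.5 | r = 0.6 | r = 0.7 |
|---|---|---|---|---|---|---|
| 30 | 0.748 | 0.763 | 0.728 | 0.661 | 0.611 | 0.545 |
| 20 | 0.940 | 0.973 | 0.928 | 0.842 | 0.778 | 0.695 |

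**Change scores are not a substitute.** A between-group comparison of change has SE = √(2/n) × √[2(1 − r)]. At N = 40 this is 0.374 for r = 0.3, 0.316 for r = 0.5 and 0.245 for r = 0.7. The ANCOVA values are 0.306, 0.278 and 0.229. The change score gains nothing at r = 0.5 and is worse than follow-up alone below that.

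**The case against.** The strongest reply is that the article is a condensed account. It never calls the comparison unadjusted, and a covariate could be named in an analysis plan that is not shown. The trial also disclaims any intention to detect a group difference, no go/no-go decision hangs on the test, and the size of the gain rests on a correlation that the article does not give.

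Much of this stands, and it rules out several stronger readings that a reader might infer:

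- **That the plan commits to an unadjusted test.** This is an inference. The text is silent on adjustment.
- **That baseline PDI is discarded.** It is used in three other ways. Only a role in the between-group estimate is unstated.
- **That T2 and T3 are tested separately between groups.** Those time points are named only in the sentence on paired comparisons with baseline.
- **That the comparison is biased or invalid.** An unadjusted randomised comparison is unbiased, and its interval already allows for chance baseline imbalance.
- **That a rank test rules out a mean difference and SD.** The article also promises descriptive results and effect sizes, which can supply both.

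The reply does not remove the point. The article does more than leave the method unstated: it fixes a rule for choosing the test and lists the uses of baseline. A descriptive purpose is no argument for a less precise estimate when estimating the effect is itself an aim.

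**Conclusion.** The point holds as one of avoidable imprecision and of an analysis left open to the data. With 40 analysed, baseline adjustment takes the 95% CI half-width from 0.64 SD to 0.56, 0.52 or 0.46 SD if r is 0.5, 0.6 or 0.7. At r = 0.3 the interval narrows by about 3%, and at r = 0 it widens by about 1.5%. Intervals are wider throughout with attrition, and the relative gain is similar.

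These figures assume equal arms, a linear baseline relationship with a common slope, and a correlation that the documents do not supply. If r is low, which is possible in patients whose condition may change quickly, the benefit is small. The possible loss is slight and the possible gain substantial, so the change is worth making.

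**What to change.** In Analyses, Quantitative data:

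1. Name ANCOVA with baseline PDI as covariate, or a mixed model for T2 and T3 with the same covariate, as the main between-group analysis.
2. Report the adjusted mean difference with its 95% CI at T2 and at T3.
3. Remove the rule that lets the observed distribution decide the main analysis. Any rank test becomes a sensitivity analysis reported alongside.
4. Apply the same adjustment to the secondary scales, each with its own baseline value. Table 1 shows that they are collected at recruitment.

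The within-group paired summaries can stay as description. Adjustment for Trust and bootstrap intervals are optional and not part of this point.

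The cost is a change of wording and one degree of freedom for the baseline covariate, which widens the interval by about 1.5% at N = 40 if baseline proves uninformative. No new data are needed.

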**Design:**

A randomised controlled open-label trial. Forty patients with advanced cancer are randomly allocated to one of two groups: (i) Intervention (Dignity Therapy offered in addition to any standard care), and (ii) Control group (standard care). Recipients of the 'generativity' documents are asked their views on taking part in the study and the therapy. Both quantitative and qualitative outcomes are assessed in face-to-face interviews at baseline and at approximately one and four weeks after the intervention (equivalent in the control group). The primary outcome is patients' sense of dignity (potential effectiveness) assessed by the Patient Dignity Inventory. Secondary outcomes for patients include distress, hopefulness and quality of life. In view of the relatively small sample size, quantitative analyses are mainly descriptive. The qualitative analysis uses the Framework method.

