## Aims and objectives

The aims of the study are to assess the feasibility, acceptability and potential effectiveness of Dignity Therapy to reduce psychological and spiritual distress in people with advanced cancer who have been referred to hospital-based palliative care teams. The specific objectives are to:

a) Determine whether Dignity Therapy is likely to increase peoples' sense of dignity or reduce psychological or spiritual distress.

b) Determine whether it is feasible to provide Dignity Therapy in this setting.

c) Determine whether Dignity Therapy is acceptable to patients and their families.

d) Pilot methods for a larger (Phase III) RCT (e.g. recruitment, randomization, follow-up, suitability of measures, effect size).

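### Paired tests against baseline in each arm are planned beside the between-arm comparison, and the protocol does not say which of them answers the effectiveness objective or supplies the Phase III effect size

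*Protocol article*

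**What the plan says.** The Quantitative data section of the protocol article describes the analysis as mainly descriptive because the sample is small. It announces comparisons both between and within participants, with effect sizes for them, and leaves the choice of parametric or non-parametric test to the distribution of the data.

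The randomised comparison comes first: "The intervention and control group will be compared on the main outcome (a sense of dignity"), and likewise on the secondary outcomes. The within-arm analysis follows: "We will also compare Time 2 and Time 3 follow-up with baseline for both groups on these measures, using a paired test". "These measures" are the main and secondary patient outcomes just listed.

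Objective (a) under Aims and objectives is: "Determine whether Dignity Therapy is likely to increase peoples' sense of dignity or reduce psychological or spiritual distress". Objective (d) and the Participants section add that the study should yield an effect size for a Phase III trial. No sentence says which of the two kinds of comparison serves either purpose.

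**The concern.** Objective (a) is a causal question, and in a randomised trial the contrast between arms answers it. A change from baseline within one arm combines any effect of the therapy with everything else that moves the score: the course of the disease, regression to the mean, the work of the palliative care team, and the research interviews. The article itself allows for the last of these. Of the controls it says: "Completing the measures and taking part in the interview gives them an opportunity to talk about their feelings", and it plans to ask them whether this was therapeutic. A change common to both arms is therefore plausible.

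If one arm's paired test is significant and the other's is not, a reader may take that as evidence that the arms differ. It is not, because the two tests never compare the arms with each other.

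The same ambiguity touches the Phase III design. If a within-arm effect size were carried forward, it would include the shared change. The article says the results will help determine whether a Phase III trial is needed, so the source of the estimate matters.

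**Working it through.** The article gives no power, alpha or effect-size calculation, so there is no planned figure to reproduce.

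**Inputs from the article**
- Total sample: "The sample will comprise 40 adults with advanced cancer" (Participants).
- Allocation: "block randomization with a fixed block size of two" (Randomization). With two arms this implies 40 / 2 = 20 randomised per arm. The figure is derived, not stated.
- Repeated patient instruments in Table 1: Patient Dignity Inventory, Herth Hope Index, Hospital Anxiety and Depression Scale, Distress Thermometer, EQ-5D, two-item quality of life, Palliative Care Outcome Scale. That is 7, at 2 follow-up times: 7 × 2 = 14 comparisons per arm, 28 in all.

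**Assumptions (not in the article)**
- Two-sided 5% paired t tests.
- All 20 per arm analysed.
- The same true change in both arms, so no therapy effect. The change is dz, in SDs of the within-patient change, and is varied from 0 to 1.0.

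**Formulas**
- p = power of one paired t test with n = 20 at shared change dz (noncentral t).
- Probability that exactly one arm is significant = 2p(1 − p).
- Probability that one named arm alone is significant = p(1 − p).

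| Shared change dz | p | Exactly one arm | One named arm only |
|---|---|---|---|
| 0 | 0.050 | 9.5% | 4.8% |
| 0.1 | 0.071 | 13.2% | 6.6% |
| 0.2 | 0.136 | 23.5% | 11.7% |
| 0.3 | 0.247 | 37.2% | 18.6% |
| 0.4 | 0.397 | 47.9% | 23.9% |
| 0.46 | 0.497 | 50.0% | 25.0% |
| 0.6 | 0.721 | 40.2% | 20.1% |
| 0.8 | 0.924 | 14.1% | 7.0% |
| 1.0 | 0.989 | 2.3% | 1.1% |

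For example, at dz = 0.3: 2 × 0.247 × 0.753 = 0.372. The expression 2p(1 − p) peaks at 50% when p = 0.5, so the risk is greatest for moderate shared change and small at either end.

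**Direction.** If both arms improve, the pattern favouring the therapy is a significant improvement in the therapy arm alone. If both decline, it is a significant decline in the control arm alone. Either way it occurs at most half as often as the one-arm-only pattern. With no change, significant improvement in the therapy arm alone has probability 0.025 × 0.95 = 2.4%. A between-arm test at the same alpha favours the therapy falsely 2.5% of the time, whatever the shared change.

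**Fewer patients analysed.** The article gives no drop-out rate. With 15 per arm, exactly one arm is significant in 9.5% (dz = 0), 31.0% (0.3) and 49.2% (0.5) of comparisons. With 10 per arm the figures are 9.5%, 23.5% and 41.4%.

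**Across the 14 pairs of tests.** The expected number with exactly one arm significant is 14 × 0.095 = 1.3 at dz = 0 and 14 × 0.372 = 5.2 at dz = 0.3. A simulation with correlations between comparisons of 0.7 down to 0 found at least one such pair in 45% to 75% of trials at dz = 0 and in 86% to 100% at dz = 0.3. These counts include either arm.

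**Effect size.** If both arms change by 0.3 SD and the therapy does nothing, the therapy arm's expected within-arm standardised change is 0.3, while the between-arm difference is 0.3 − 0.3 = 0.

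**The case against.** The strongest reply is that the valid analysis is already planned. The between-arm comparison covers the same outcomes, comes first in the section, and the paired tests are introduced as an addition. This stands. A reader might infer that the plan lacks a randomised comparison, or that it will judge the therapy by the paired tests. The text supports neither: no rule ties a conclusion to the within-arm results.

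The study is also a pilot. The Participants section says it was not planned to detect significant group differences, and no alpha or success criterion is given. This limits the severity. It also leaves little reason for 28 within-arm significance tests.

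Within-arm change has proper uses here: checking whether the measures suit the setting, describing the longer term, and exploring whether the control interviews help. This stands too, but estimates of change with their spread serve those uses without a p-value.

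A reader might further infer that the paired tests falsely favour the therapy in roughly 19% to 25% of comparisons, against 2.5% for a between-arm test. That is too strong. The rate needs a shared change of about 0.3 to 0.5 SD, which the article does not give. For significance in the therapy arm alone to favour the therapy, both arms must also be improving.

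Finally, if both arms decline and the therapy slows the decline, the planned between-arm comparison already addresses that, so the paired tests do not create a false negative there.

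**Conclusion.** The point holds as a minor one. The article fixes paired tests in each arm, promises effect sizes for both kinds of comparison, and does not say which answers objective (a) or supplies the Phase III effect size. This is a stated choice, not a detail left to an analysis plan that is not shown.

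How often a misleading pattern would appear rests on the assumed alpha, the 20 analysed per arm and a shared change that the article does not quantify. It runs from about 9.5% per comparison with no change, through 23% to 50% at 0.2 to 0.6 SD, to about 2% at 1.0 SD. The part that favours the therapy is at most half of this. The point covers only the repeated patient measures, not the family and friends' measures.

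**What to change.** In the Quantitative data section, replace the paired tests with a description of change by arm at T2 and T3: mean and SD, or median and IQR, without significance tests. State that conclusions on potential effectiveness, and the effect size for Phase III, rest only on the between-arm difference at T2 and T3, adjusted for the baseline score, with its 95% CI.

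The baseline scores are already collected, so the change needs no new data or visits, only wording. The one loss is the within-arm p-values.
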